## Abstract

**Background:**

Exercise during haemodialysis improves strength and physical function. However, both patients and clinicians are time poor, and current exercise recommendations add an excessive time burden making exercise a rare addition to standard care. Hypothetically, blood flow restriction exercise performed during haemodialysis can provide greater value for time spent exercising, reducing this time burden while producing similar or greater outcomes. This study will explore the efficacy of blood flow restriction exercise for enhancing strength and physical function among haemodialysis patients.

**Methods:**

This is a randomised controlled trial design. A total of 75 participants will be recruited from haemodialysis clinics. Participants will be allocated to a blood flow restriction cycling group, traditional cycling group or usual care control group. Both exercising groups will complete 3 months of cycling exercise, performed intradialytically, three times per week. The blood flow restriction cycling group will complete two 10-min cycling bouts separated by a 20-min rest at a subjective effort of 15 on a 6 to 20 rating scale. This will be done with pressurised cuffs fitted proximally on the active limbs during exercise at 50% of a pre-determined limb occlusion pressure. The traditional cycling group will perform a continuous 20-min bout of exercise at a subjective effort of 12 on the same subjective effort scale. These workloads and volumes are equivalent and allow for comparison of a common blood flow restriction aerobic exercise prescription and a traditional aerobic exercise prescription. The primary outcome measures are lower limb strength, assessed by a three repetition maximum leg extension test, as well as objective measures of physical function: six-minute walk test, 30-s sit to stand, and timed up and go. Secondary outcome measures include thigh muscle cross sectional area, body composition, routine pathology, quality of life, and physical activity engagement.

**Discussion:**

This study will determine the efficacy of blood flow restriction exercise among dialysis patients for improving key physiological outcomes that impact independence and quality of life, with reduced burden on patients. This may have broader implications for other clinical populations with similarly declining muscle health and physical function, and those contraindicated to higher intensities of exercise.

**Trial registration:**

Australian and New Zealand Clinical Trial Register: ACTRN12616000121460.

## Background

End-stage kidney disease (ESKD) is the 5th stage of chronic kidney disease, characterised by a failure of the kidneys to adequately filter blood [1]. ESKD is estimated to affect as many as 2 million people worldwide, approximately half of whom do not receive adequate treatment [2, 3]. Treatment requires either transplantation, or if transplantation is unavailable patients are solely reliant on regular dialysis [4]. Largely due to the regularity of dialysis as a treatment, ESKD is among the most common reasons for hospitalisation [2]. However, despite dialysis being considered one of the most efficacious means of treating ESKD, it does not guarantee that life can be sustained, with 12 month mortality rate following initiation of dialysis estimated to be 10–12% [5].

ESKD patients suffer from anaemia, fatigue, muscle atrophy, decreased aerobic capacity, reduced participation in physical activity, increased risk of falls, and decreased quality of life [4, 6–8]. Patients with ESKD also demonstrate significant decline in physical function and tasks reflective of activities of daily living [9–13]. This diminished physical function leads to a significant loss of independence with 95% of people with ESKD not fully independent and in need of assistance with at least one activity of daily living (ADL) [14]. This is more significant considering that an inability to independently complete ADLs is a major predictor of mortality for ESKD [14]. Exercise is well tolerated among patients with ESKD and is an efficacious method for ameliorating these adverse symptoms characteristic of ESKD [15–18].

Heterogenous methodology, prescription and reporting among ESKD exercise studies make it difficult to draft guidelines on the dosage and mode of exercise training to derive the best outcomes for ESKD patients [8, 19]. The current guidelines for exercise training with ESKD recommend it encompasses aerobic (4 sessions; 45 mins), resistance (2 sessions; 20 mins), and flexibility (7 sessions; 10 mins) exercise [20]. The cumulative time commitment for these recommendations is substantial, and would require training on both dialysis (during first 2 h of dialysis) and non-dialysis days [20]. However, most randomised controlled trials examining exercise regimens in ESKD have only utilised aerobic training, most commonly stationary cycling [20]. Aerobic exercise training alone does not traditionally increase strength and hypertrophy, nor produce significant improvements in physical function, all of which are needed among this population [21].

Adherence to exercise training programs, regardless of aerobic, resistance or combined modalities, is also poor among ESKD patients, with more than 20% choosing not to participate, citing issues such as lack of time, lack of energy, too much trouble, and resistance training being too difficult [22]. Of those that chose to participate in exercise training, the dropout rate was more than 25% for programs utilising exercise training on non-dialysis days [22]. While there is still an increased dropout rate among patients with ESKD when exercise is completed intradialytically (approximately 17%) [22], it is lower than that seen on non-dialysis days. This suggests that intradialytic exercise is still preferable with regards to participant retention than exercise on non-dialysis days.

Resistance training poses further complications in the setting of a dialysis unit as the required equipment is cumbersome, and poses a high risk for cross-infection. Less cumbersome washable elastic resistance bands may be one option [23]. Exercise training during dialysis also needs to be completed in the first 2 h of dialysis sessions [24]. Therefore, finding a solution that may provide improvements in all key outcomes as efficiently as possible, allowing for completion during dialysis would be preferable.

Blood flow restriction exercise training uses pressurised cuffs fitted proximally on the active limbs during exercise training, and can elicit the above benefits at lower exercise intensities than non- blood flow restriction training [25, 26]. Blood flow restriction may be one method for achieving outcomes reflective of both resistance, and aerobic exercise training while providing an efficient, simple exercise prescription model in the dialysis setting. Blood flow restriction aerobic exercise training has been shown to increase muscle size and strength more than equivalent-intensity non-blood flow restriction aerobic exercise training, while still providing comparable or greater improvements in cardiovascular fitness [25, 27, 28].

While blood flow restriction exercise training is used predominately in single joint isolation resistance training exercises such as knee extension, it has also been applied during aerobic exercise training such as walking or cycling [25, 29–32]. Common blood flow restriction aerobic exercise training protocols utilise short exercise durations of 10 to 20 min [25, 32–34]. Such studies utilising blood flow restriction with aerobic exercise training have demonstrated increases in lower limb muscle volume and strength of up to 8% and 16%, respectively [25, 32, 33]. However, it should be noted that without blood flow restriction, low-intensity aerobic exercise training is generally insufficient to increase muscle volume or strength, unless there is previous muscle atrophy or the initial level of participant physical activity is extremely low [35]. Even in such instances, improvements in muscle volume and strength are unlikely to be of similar magnitude as seen with blood flow restriction [35].

Regardless of the presence of blood flow restriction, aerobic exercise training improves aerobic fitness provided that the exercise is of sufficient intensity [36]. Indeed, studies have demonstrated that low-to-moderate intensity blood flow restriction aerobic exercise training is able to increase aerobic capacity when exercising at intensities equivalent to 40% of peak exercise oxygen consumption (⩒O_2_peak) [32, 33, 37].

Studies examining the haemodynamic responses to blood flow restriction identify blood flow restriction aerobic exercise training as having lower haemodynamic stress than high intensity resistance training, while providing similar outcomes [38–40]. As such, blood flow restriction is purported to be a potentially beneficial addition to exercise for clinical populations who may be contraindicated to high-intensity resistance training. While blood flow restriction exercise is a novel addition to exercise among ESKD patients, pilot data from this laboratory (unpublished) indicates that haemodynamic responses (systolic blood pressure, diastolic blood pressure, mean arterial pressure, heart rate) do not differ markedly between low-intensity blood flow restriction and non-blood flow restriction aerobic exercise both performed during haemodialysis in this population.

Aerobic capacity and muscle strength are both key physiological factors underpinning physical function [41] and both can improve with blood flow restriction aerobic exercise training. As declines in physical function, muscle strength, and aerobic capacity, as well as accelerated muscle atrophy are common among patients with ESKD, blood flow restriction aerobic exercise training may present an opportunity to increase the efficiency of time spent exercising for this population.

This study will examine the efficacy of blood flow restriction aerobic training among patients with ESKD on haemodialysis (HD). We hypothesise that blood flow restriction aerobic exercise training will improve physical function, muscle strength, and muscle size among patients with ESKD beyond that of traditional aerobic exercise training.

## Methods

### Design

This is a 12-week randomised controlled trial consisting of three groups randomised to exercise or usual care (Fig. 1). Participants will be randomised to one of three groups: a blood flow restriction cycling exercise training group (BFR-C), a non-blood flow restriction cycling exercise training group (CYC), or a non-exercising, usual care control group (CON).

**Fig. 1 Fig1:**
[figure not shown]
Study Flow Chart. BFR-C – Blood flow restriciton cycling group; CYC – Traditional cycling group; CON – Usual care control group; LOP – Limb occlusion pressure; 3RM LE – Three-repetition Maximum Leg Extension; 6MWT – 6 min walk test; STS30–30-s sit-to-stand test; TUG – Timed up and go; pQCT – Peripheral Quantitative Computed Tomography; iDXA – Dual X-ray Absorptiometry; URR – Urea Reduction Ratio; Hb – Haemoglobin; Alb – Albumin; K^+^ − Potassium; PTH – Parathyroid Hormone; PO4 – Phosphate; RPE – Rating of perceived exertion

### Sample size calculation

The most relevant outcome for blood flow restriction training studies is knee extensor muscle strength, and this was used as the main primary outcome measure for calculating required sample size. Based on data from previous blood flow restriction research [25, 29, 32, 33], and previous exercise for ESKD research [18, 42, 43], the projected percentage changes in knee extensor muscle strength for each of the three groups are CON = −3%, CYC = 2%, BFR-C = 12%. The common standard deviation within group, based on the prior research was determined to be 15. Thus, to achieve a power of 80% at an α level of 0.05, 20 participants per group will be required to detect a difference between the expected means for percentage strength improvement. However, based on previous work conducted by this research group a conservative attrition rate of 20% is expected over 3 months due to voluntary patient withdrawal, death, additional hospitalisation, transfer to another facility, or patients receiving transplants [23]. Thus, a total of 75 participants will be recruited and randomly allocated to one of the three groups.

### Recruitment and screening of participants

Participants will be recruited through recommendation and referral from treating physicians at a number of dialysis clinics linked to a major public hospital service in a large metropolitan Australian city. Additionally, nurse unit manager recommendations and fliers briefly outlining the study posted within the dialysis clinics will be used to help identify prospective participants. Prospective participants will be screened initially face-to-face or via telephone by a member of the research team. Following this, confirmation from the treating physician will be obtained if not implied by referral. Participants will be required to provide written, informed consent prior to participation in the study.

### Inclusion and exclusion criteria

Eligible participants will be male and female stable chronic (>3 months) haemodialysis patients aged between 18 and 80 years. Participants will be deemed medically eligible by their treating physician before participation in the present study. Participants will be excluded if they do not understand English and are unable to complete or comprehend the surveys or study documents; if within the previous 12 weeks they have participated in regular physical activity or sport (>150 min.wk.^−1^) of moderate or greater intensity [44], or structured resistance training (> 1 session.wk.^−1^); if they have symptomatic peripheral vascular disease, limb ischemia, untreated symptomatic cardiovascular disease, or any other absolute contraindications to exercise training (such as musculoskeletal factors or neurological conditions) that may affect their ability to perform physical assessments or exercise training protocols in the present study; if they are currently smokers; or if they are pregnant or have required hospitalisation for non-dialysis reasons in the 4 weeks prior to the study’s commencement. Patients will also be deemed unable to exercise during individual dialysis sessions if they present with fluid overload (> 5% above dialysis base weight) as this can cause reduced cardiovascular reserve [45]. Similarly, if patients have systolic blood pressure > 180 mmHg, or diastolic blood pressure < 90 mmHg prior to exercise they will be deemed unsuitable for exercise on that day (excluding the first blood pressure reading before dialysis, which is known to be unreliable) [46]. Of clinical concern is the known propensity for HD patients to become hypotensive (potentially more so post-exercise) during dialysis [47]. Although this is uncommon and our pilot data indicates this is not exacerbated by blood flow restriction, to ensure the safety of all patients they will be monitored for chest pain/discomfort, dyspnoea, lower limb pain, symptoms of severe hyper- or hypotension, and other signs of adverse events, which will be reported to the ethics committee of both the treating hospital and Deakin University.

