### Exercise intervention

Exercise training sessions will occur intradialytically for all exercising participants and will be completed within the first 2 h of the session to avoid loss of exercise training quality [24, 48]. All sessions will be supervised by a member of the research team. Exercise training sessions will consist of cycle exercise for both BFR-C and CYC groups. Both BFR-C and CYC groups will complete a total volume of 20 min cycling at a relative intensity for each participant to be dictated by rating of perceived exertion (RPE), similar to previous exercise and ESKD studies [17, 49, 50]. This will also be compared to measurements of percentage age-predicted maximum heart rate (APHR_max_) in order to determine if targeted RPE needs to be adjusted to account for potential discrepancies between patient subjective intensity and objectively observed intensity. If participants are unable to maintain the prescribed cadence at this workload for the full duration, they will be instructed to complete as much of each cycling bout as possible.

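### The pre-exercise safety rule bars patients whose diastolic pressure is below 90 mmHg, so it stops ordinary readings and sets no upper diastolic limit

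*Protocol article*

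**What the plan says.** The Inclusion and exclusion criteria section of the Protocol article includes a blood pressure check before each exercise session. A patient does not exercise that day if "systolic blood pressure > 180 mmHg, or diastolic blood pressure < 90 mmHg prior to exercise they will be deemed unsuitable for exercise". The only reading set aside is the earliest one: "excluding the first blood pressure reading before dialysis, which is known to be unreliable".

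The next sentence turns to low pressure: "Of clinical concern is the known propensity for HD patients to become hypotensive (potentially more so post-exercise) during dialysis". The section then says of patients that "they will be monitored for chest pain/discomfort, dyspnoea, lower limb pain, symptoms of severe hyper- or hypotension", among other signs of adverse events.

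The Exercise intervention section adds that "All sessions will be supervised by a member of the research team". The planned exposure is given in the abstract: "Both exercising groups will complete 3 months of cycling exercise, performed intradialytically, three times per week". The Design section gives the length as 12 weeks.

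**The concern.** A pre-exercise pressure screen should stop patients whose pressure is too high, too low, or both. The two halves of this rule do not fit together. The systolic half is an upper limit, as expected for a hypertension screen. The diastolic half is a lower limit, set at a value that most ordinary readings fall below.

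Two things are at stake. The first is safety: nothing in the rule stops a patient with high diastolic pressure whose systolic pressure is 180 mmHg or less. The second is delivered dose: if staff apply the rule as printed, most sessions in both exercise arms would be withheld. The strength gains assumed in the sample size calculation (12% for BFR-C, 2% for CYC) presuppose that the training takes place.

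**Working it through.** **Reading the rule.** The two conditions are joined by *or*, so exercise is allowed only when systolic is at most 180 mmHg and diastolic is at least 90 mmHg.

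| Reading | Systolic > 180? | Diastolic < 90? | As printed |
|---|---|---|---|
| 120/80 | no | yes | barred |
| 175/115 | no | no | allowed |

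Any patient with systolic below 90 mmHg also has diastolic below 90 mmHg. The printed rule therefore does stop hypotensive patients, but only by stopping nearly everyone else as well.

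**Looking for a correction elsewhere.** The rule appears once. Symptom monitoring and session supervision are stated, but neither supplies a pressure threshold that could replace it.

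**Which limit was meant.** Two repairs are plausible, and they give different rules.

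- *Reversed sign:* diastolic above an upper limit. This pairs naturally with systolic > 180 mmHg as a hypertension screen.
- *Wrong variable:* systolic < 90 mmHg. This fits the sentence on hypotension that follows, and gives a systolic window from 90 to 180 mmHg.

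Both allow 120/80. They differ on 175/115: the first bars it if the upper limit is below 115, and the second allows it. They also differ on a patient with systolic below 90 mmHg: the first would normally allow exercise, and the second bars it. The monitoring text, which covers "symptoms of severe hyper- or hypotension, and other signs of adverse events", does not settle the matter because it names both extremes.

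**Illustrating the size.** The article gives no blood pressure distribution. The means and SDs below, and normality, are assumptions.

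- Planned sessions: 3 per week × 12 weeks = 36.
- Proportion barred by the diastolic term: P(DBP < 90) = Φ((90 − mean)/SD).
- Sessions withheld: 36 × P. Sessions left: 36 × (1 − P).

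| Assumed mean / SD (mmHg) | (90 − mean)/SD | P(DBP < 90) | Withheld of 36 | Left |
|---|---|---|---|---|
| 70 / 10 | 2.00 | 0.977 | 35.2 | 0.8 |
| 70 / 15 | 1.33 | 0.909 | 32.7 | 3.3 |
| 80 / 10 | 1.00 | 0.841 | 30.3 | 5.7 |
| 80 / 15 | 0.67 | 0.748 | 26.9 | 9.1 |
| 85 / 10 | 0.50 | 0.691 | 24.9 | 11.1 |
| 85 / 15 | 0.33 | 0.631 | 22.7 | 13.3 |

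More than half of the sessions are lost in every row. If only the sign were reversed and 90 mmHg kept as the limit, the proportion barred would be 1 − P, about 2% to 37% over the same range.

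The calculation takes one deciding reading per session. The article does not say which reading after the first one decides.

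**The case against.** The strongest reply is that this is a slip of the pen in a condensed article. Nobody decided to train only patients with diastolic pressure of 90 mmHg or more. A research team member supervises every session, an exercise physiologist adjusts the workload session by session, and perceived exertion is tracked as a rolling two-week average. A rule that cancelled most sessions would be noticed within days, so the larger the computed loss, the less likely it is to happen. The session counts rest on assumed pressures. The safety gap is partly covered by the systolic limit, physician clearance, the exclusion of untreated symptomatic cardiovascular disease, and symptom monitoring. The sample size, randomisation, outcomes and analysis are untouched.

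Much of this stands. The error is probably clerical, sustained literal use is unlikely, and the session counts are illustration, not evidence from the trial. It does not remove the defect. The article states numeric limits and one of them is wrong; a fuller document may excuse what is left out, but not a limit that is misstated. Noticing the slip does not tell staff which repair to make, and patients come from a number of dialysis clinics, so informal corrections could differ. None of the other safeguards sets a diastolic limit.

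**Conclusion.** The concern holds. The diastolic term is wrong as printed, in direction or in variable, and the article contains no correct version. This follows from the text alone and depends on no assumed figure.

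The effect on dose is conditional: if staff followed the rule literally, and with the assumed means, SDs and normality, about 23 to 35 of 36 sessions would be withheld and 1 to 13 would remain. The more credible harm is narrower. The published pre-exercise limit cannot be used, and the intended one cannot be recovered from the text. The rule applies alike to BFR-C and CYC, so no bias between these two arms is claimed. It should be fixed because it governs participant safety.

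**What to change.** Before training starts, replace the diastolic term with the limit intended: either systolic below 90 mmHg, as a hypotension limit, or diastolic above a stated upper limit. The medical lead should confirm the choice against the source cited for the rule. If the systolic version is chosen, there will still be no upper diastolic limit, and the medical lead should be content with that. Notify the ethics committee of the correction.

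It is also useful, though not essential to the correction, to log each session withheld under the rule and report the count by arm. If training has already begun, correct the rule at once and count the sessions already withheld.

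The cost is a one-line amendment, an ethics notification and, if the log is kept, one extra field in the session record.

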### Randomisation

Randomisation will be conducted at a participant level prior to familiarisation and baseline testing, and will randomise participants by blocks of 4 via a computer-generated random number sequence by an independent researcher. Blinding of intervention group to clinical staff and participants will not be possible once the intervention commences.

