#### Blood flow restriction procedure

Blood flow restriction will be applied using an automatic tourniquet system (A.T.S 3000, Zimmer Inc., OH, USA). The ATS produces a defined, controlled pressure via adjustable pneumatic cuffs (52 cm long, 10.5 cm wide; bladder length 45 cm, bladder width 8 cm). The pressure is regulated to control for changes in muscle contractile pressures under the cuff in such a way that the occlusive pressure applied to the limb is constant.

The cuffs will be applied to the proximal aspect of the thigh prior to commencing exercise, and gradually inflated, as detailed by Abe et al. (2006) [25]. Blood flow restriction pressure will be set at 50% of pre-exercise resting LOP. LOP will be calculated during a familiarisation session for participants allocated to the BFR-C group using a digital plethysmograph (Pulse Sensor, Zimmer ATS 3000) applied to the second toe [40, 53]. A seated or recumbent posture will be used for LOP as it most closely matches the posture that will be used during the exercise training sessions. To determine LOP, the pneumatic cuffs are inflated to the point at which the plethysmograph can no longer detect blood flow to the toe (blood flow completely occluded). This will be done for each leg and repeated to ensure accuracy (<20 mmHg), and an average of these measures will be taken. The 50% LOP that is to be applied during exercise training sessions does not fully occlude the limb in this manner, and allows for continuous blood flow during exercise.

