### Data collection

Data collection will occur at baseline (T_1_) and 12 weeks (T_2_), with testing to be completed at the treating HD unit prior to the commencement of the participants’ HD session. Personal information, including relevant medical history will be collected prior to the initiation of testing or intervention upon receiving participant consent. This will include patient characteristics of age, gender, time in months that the participant has been receiving HD (dialysis vintage), basic anthropometric measures (height, weight, and BMI), relevant comorbidities and medications, transplant status, and type of dialysis access. Some or all of which may be taken, with approval, from the case file at the HD unit. The remaining data collected will include all measures of muscle function and physical function. Body composition scans will be performed on a non-dialysis day, separate from other testing procedures for participants who opt-in to this aspect of testing. Additional pathology measurements will include haemoglobin, albumin, potassium, parathyroid hormone, phosphate, urea reduction ratio (URR), creatine kinase and lactate. These measures will occur as part of routine pathology tests where possible, or will be requested out-of-cycle to coincide with the necessary period of the training intervention. Data will be coded and stored securely at Deakin University. Data collected from those who withdraw from the study will not be used for statistical analyses. This has been accounted for when completing the power analysis, with an additional 20% added to the target sample size. Attrition may be for a number of reasons, which will be ascertained upon withdrawal where possible.

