### Primary outcome measures

#### Lower-limb muscle strength

Maximal lower limb muscle strength will be determined using three-repetition maximum (3RM) knee extension (HS-LE, Life Fitness, Victoria, Australia) [57]. A 3RM knee extension test measures the maximum weight that can be lifted for three consecutive repetitions of a knee extension exercise with good technique and full range of motion. The 3RM result will be input into a formula to derive equivalent one-repetition maximum for each participant [58].

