#### Physical function

Objective physical function will be measured using the 30-s sit to stand test (STS30), the timed up and go test (TUG), and the six-minute walk test (6MWT).

The STS30 measures lower limb muscle strength and function and requires participants to stand from a chair and then return to the seated position as many times as possible in 30 s [59]. The test has also displayed strong comparative validity to lower extremity 1RM strength testing, particularly among community-dwelling older adults [59]. It has also demonstrated a high level of reliability among ESKD patients undergoing HD (ICC = 0.93) [60].

The TUG is a measure of dynamic balance and mobility requiring participants to stand from a chair, walk to and then around a cone placed 3 m away, walk back to the chair, and sit back down as quickly as possible. This test will be repeated three times, and an average time taken for accuracy purposes [61]. The TUG strongly reflects gait speed among older adults, and has shown strong test re-test reliability not only among older adults, but in ESKD patients undergoing HD (ICC = 0.91–0.96) [62–64].

The 6MWT is a self-paced assessment of aerobic capacity, and a strong index of all cause morbidity in older adults [65]. It requires participants to walk laps of a straight 30 m course with the objective to cover as much distance as possible in the six-minute duration [65]. The 6MWT is a reliable measure for patients with ESKD (ICC = 0.93–0.96) [60, 66]. It has also been validated against ⩒O_2_max for patients with ESKD, with moderate strength coefficients of correlation (*r* = 0.56–0.73) [11, 67].

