#### Symptom related quality of life

The POS-S Renal questionnaire will be given to patients during the familiarisation session to assess their quality of life in direct relation to the symptoms experienced as a part of their condition [69]. This questionnaire provides valuable feedback about any changes experienced by patients regarding quality of life and disease-specific symptoms as a result of the intervention.

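### Randomisation comes before familiarisation and baseline testing, and an arm-specific step at familiarisation can reveal the blood flow restriction arm before the effort-dependent baselines are taken

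*Protocol article*

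**What the plan says.** The Randomisation section fixes the order of events: "Randomisation will be conducted at a participant level prior to familiarisation and baseline testing". It adds: "Blinding of intervention group to clinical staff and participants will not be possible once the intervention commences".

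The section on the blood flow restriction procedure places an arm-specific step early: "LOP will be calculated during a familiarisation session for participants allocated to the BFR-C group". For this measurement, thigh cuffs are inflated until a toe sensor no longer detects flow. It is done on each leg and repeated.

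The symptom questionnaire belongs to the same stage: "The POS-S Renal questionnaire will be given to patients during the familiarisation session".

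The primary outcomes, measured at baseline (T1) and 12 weeks (T2), are a strength test and three function tests. For strength, "Maximal lower limb muscle strength will be determined using three-repetition maximum (3RM) knee extension". For the six-minute walk (6MWT), "The 6MWT is a self-paced assessment of aerobic capacity". The 30-s sit to stand (STS30) counts as many repetitions as the participant can manage, and the timed up and go (TUG) is done as fast as possible.

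The Sample size calculation section powers the trial on percentage change in knee extensor strength: −3% in usual care (CON), 2% in CYC and 12% in BFR-C, with a standard deviation of 15.

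**The concern.** A baseline protects a comparison of change because it is fixed before anyone can know the arm. Here it is taken after allocation. A participant who has just had cuffs inflated to full occlusion can infer the arm, and so can whoever did it. If that knowledge changes how hard the participant tries, or how the tester encourages, the T1 value differs between arms for a reason unrelated to strength or fitness. The same applies to self-reported symptoms.

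In a percentage change, baseline is both the value subtracted and the divisor, so any such difference carries over into the quantity on which the trial is powered.

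**Working it through.** **1. Sequence.** Reading the sections together gives: randomise; familiarise, with LOP measured in BFR-C only and the POS-S Renal questionnaire given; T1 tests; start training. The Randomisation section names familiarisation before baseline testing, which suggests that LOP comes first. The article does not spell out the exact order of LOP and the T1 tests, and Fig. 1 is not shown. Hence the wording before or around T1.

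**2. The plan's own figures.** Inputs from the Sample size calculation section: means −3, 2 and 12; SD 15; α 0.05; 20 per group; 20% attrition.
- Grand mean = (−3 + 2 + 12)/3 = 3.67.
- Cohen's f = √[((−6.67)² + (−1.67)² + 8.33²)/3]/15 = 6.24/15 = 0.416.
- Power of the one-way ANOVA F test for three groups: 0.786 at 19 per group and 0.809 at 20. So 20 per group is reproduced.
- 60/(1 − 0.20) = 75. The total is reproduced.

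These figures are not in dispute. The planned BFR-C versus CYC difference is 12 − 2 = 10 points.

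**3. Effect of a shifted baseline on percentage change.** If T1 is under-measured by a fraction s in one arm and there is no true change, the apparent change is 1/(1 − s) − 1.
- s = 0.03: 1/0.97 − 1 = 3.1 points, or 31% of the planned 10.
- s = 0.05: 1/0.95 − 1 = 5.3 points, or 53% of the planned 10.

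If T1 is over-measured, the sign reverses: 1/1.05 − 1 = −4.8 points for 5%.

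If both exercise arms are under-measured by 5% and the planned changes are true, BFR-C shows 1.12/0.95 − 1 = 17.9% and CYC shows 1.02/0.95 − 1 = 7.4%. The difference is 10.5 points instead of 10, so the shift nearly cancels in that contrast. It does not cancel against CON.

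**4. False-positive rate.** Assume no true change in any arm, 20 per group, SD 15 and one arm under-measured at T1. The omnibus F test at 0.05 then rejects with these probabilities:

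| Under-measurement in one arm | Apparent gain (points) | Probability of rejection |
|---|---|---|
| 2% | 2.0 | 0.07 |
| 5% | 5.3 | 0.18 |
| 10% | 11.1 | 0.65 |

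Every value of s is an assumption. The documents give no information on how much effort would change with knowledge of the arm. The Statistical analysis section names one-way ANOVA without saying whether it is applied to change; the figures assume that it is applied to the percentage change used for sample size.

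**The case against.** The strongest reply is that randomising early is not the same as disclosing early. An independent researcher generates the sequence, and the article says that blinding fails only when the intervention starts, which is compatible with concealment until then. An article may also leave such details to the full protocol. This stands in part: nothing shows that CYC or CON participants learn their arm before T1, and it would go too far to say that all baselines are unmasked. It does not stand for BFR-C, where LOP measurement at familiarisation acts on the allocation. The point rests on that stated order, not on a missing detail.

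A reader might infer more in several places, and the documents do not support it:
- **Scans.** It is tempting to say that muscle-size results will come from subsets self-selected by arm. The Data collection section describes scans as "separate from other testing procedures for participants who opt-in to this aspect of testing" and gives no time for the choice. Written consent precedes participation, so the choice may be made there.
- **Questionnaires.** Only the POS-S Renal is placed at familiarisation. No time is given for the CHAMPS activity survey.
- **Baseline adjustment.** One might say that adjusting for a contaminated baseline makes matters worse. If a shift d affects only T1, the change score carries d, an adjusted analysis carries about slope × d, and a follow-up-only comparison carries none. With a slope below 1, adjustment does better than the change score, though it does not remove the bias. The article plans no baseline adjustment.
- **Early leavers.** Participants may leave on learning their arm, before any baseline exists. But the Data collection section drops withdrawals from the analysis anyway, so having their baseline would not alter the analysis as written. Reordering helps only where they leave before being randomised.

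Finally, participants are unblinded at T2 whatever the sequence, so effort bias at follow-up remains.

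**Conclusion.** The concern holds in limited form. Randomisation before baseline is explicit, and the LOP step can reveal BFR-C before or around the T1 effort tests and the POS-S Renal. The text supports a baseline that can depend on the arm; it does not show that it will.

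The 3.1 to 5.3 points show how sensitive the powered quantity is; they do not estimate the bias. They rest on an assumed 3% to 5% shift confined to one arm, and the direction is unknown. Confidence is high on the order of randomisation and moderate on disclosure. The change is worth making because the threat is to the primary comparison and is cheap to avoid.

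**What to change.** After consent, record the scan opt-in, then complete a common familiarisation for all participants, every T1 test and the questionnaires. Only then randomise, or release an allocation already generated. Measure LOP in BFR-C in a separate step after allocation and before the first training session. Revise the Randomisation, Blood flow restriction procedure and Symptom related quality of life sections to match.

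The cost is one additional set-up step for BFR-C, and some patients tested at baseline who are never randomised. Sample size and endpoints do not change. The reordering protects T1 only.
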